### Primary Hypotheses

It is hypothesized that meaningful improvements (defined here as pre- to posttreatment change with at least a medium Cohen *d* effect size of 0.5) will be demonstrated on measures of eating disorder psychopathology as a result of treatment addressing binge eating and other disordered eating behaviors. It is also hypothesized that a history of trauma and current posttraumatic stress disorder (PTSD) symptoms will moderate treatment effects, in that improvements in eating disorder symptoms will be less marked among those with a history of trauma or current PTSD symptoms. Although some studies have found that PTSD does not result in poorer treatment outcomes for binge eating [19,20], other studies have found that PTSD predicts more binge eating at end of treatment [21] and premature treatment dropout for patients with BN [22]. Given these mixed findings and the assumed increased level of severity in the current population seeking higher level of care treatment, PTSD will be examined as a moderator.

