The Dysfunctional Attitudes Scale – Short Form (DAS-SF 1) [43] is a 9-item measure assessing dysfunctional attitudes of individuals with depression. Items are scored on a 4-point scale from “totally disagree” to “totally agree.” The measure is highly correlated with the original 40-item version of the DAS and has good internal consistency [43].

The PTSD Checklist for DSM-5 (PCL-5) [44] is a 20-item self-report measure that assesses the DSM-5 [1] symptoms of PTSD over the previous month. There are four subscales that correspond to PTSD symptom clusters B (intrusions), C (avoidance), D (negative alterations in cognitions and mood), and E (alterations in arousal and reactivity). It has demonstrated good internal consistency, test-retest reliability, and convergent and discriminant validity among veterans [45]. It has not yet been validated in an eating disorder population. The PCL-5 will be examined as an outcome, but also as a predictor variable to determine whether patients with higher PCL scores have poorer outcomes compared to those with lower PCL scores.

The Adverse Childhood Experiences Survey (ACES) [46] is a 10-item self-report measure that assesses 10 types of childhood trauma, including physical, verbal, or sexual abuse, physical or emotional neglect, having a parent who struggles with alcoholism, having a mother who is a victim of domestic violence, having a family member in jail, having a family member diagnosed with a mental illness, and having a family member unavailable due to divorce, death, or abandonment. Adverse childhood experiences (ACEs) have been found to be related to a number of psychiatric and medical illnesses in adulthood, often with a dose-response relationship wherein risk for illness in adulthood is related to a greater number of ACEs in childhood [46]. The ACES will be examined primarily as a predictor variable to determine whether patients with more ACEs have poorer outcomes compared to those with fewer or no ACEs.

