### A Priori Analytic Plan

All data at admission, discharge, and 3, 6, and 12 months postdischarge will be aggregated for the full sample and examined for patterns of missingness, outliers (>3 standard deviations from mean), and normality of distributions. Our a priori assumptions are that data will be missing at random, and all data will be normally distributed with the appropriately minimal proportion of outlier data points. Mixed models will be used to examine fixed and random effects of linear within-person change in BDI-II, EDQOL, OCI-R, STAI, RSE, DAS-SF, PCL-5, BES, and NEQ across our major timepoints of interest (admission, discharge, and 12-month follow-up). Mixed models will be run both unadjusted, as well as adjusted for person-level variables of BMI at admission, demographic variables of age, race/ethnicity, and gender, and diagnosis. Lastly, to examine the potential for different trajectories within-treatment and posttreatment, nested model comparisons will be conducted comparing the linear mixed models described above with mixed models including a quadratic time variable. Based on an expected effect size of at least *d*=0.5, and to account for a range of potentially inflated intraclass correlation coefficients that could reduce power, a sample size of 100 was determined to be sufficient to test both the mixed effects main effect hypotheses above, as well as the mixed effects 2-level interactions specified below.

All data at each of these timepoints will also be subset by patients above and below the threshold for history of trauma (defined as an ACES score ≥4) and above and below the most commonly established threshold for clinically significant levels of PTSD symptoms via the PCL-5 (PCL-5 ≥33) [48]. These subsets of patients will be compared using independent-samples *t* tests to determine any differences in point-prevalence of BDI-II, EDQOL, OCI-R, STAI, RSE, DAS-SF, BES, and NEQ by history of trauma or current trauma symptoms, and traditional moderation analyses with interaction terms added to the mixed models described above to determine any differences in changes over time of BDI-II, EDQOL, OCI-R, STAI, RSE, DAS-SF, BES, and NEQ by history of trauma or current trauma symptoms.

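### Both trauma moderators are dichotomised for a primary hypothesis, at a cost in information, and the PCL-5 group is not dated to admission

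*Protocol article*

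**What the plan says.** Primary Hypotheses (Protocol article) includes the expectation that eating disorder symptoms will improve less in patients with a trauma history or with current PTSD symptoms. The A Priori Analytic Plan sets out how this is tested: "All data at each of these timepoints will also be subset by patients above and below the threshold for history of trauma", with trauma history meaning an ACES score of 4 or more, and in parallel by PCL-5 at 33 or more, a cut for which a source is cited. The subsets are compared by t tests on scores at the timepoints and by interaction terms in the mixed models.

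The Measures section describes the two scores differently. On the PCL-5: "The PCL-5 will be examined as an outcome, but also as a predictor variable", the aim being to see whether higher scorers do worse than lower scorers. On the ACES, it asks whether patients with more adverse experiences do worse than those with fewer or none, and it cites a dose-response background in which "risk for illness in adulthood is related to a greater number of ACEs in childhood".

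On size, the analytic plan states that "a sample size of 100 was determined to be sufficient to test both the mixed effects main effect hypotheses above". It makes the same claim for the moderator interactions.

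Table 1 schedules the PCL-5 at baseline, discharge, 6 months and 12 months. Secondary Hypotheses expects it to improve meaningfully, which Primary Hypotheses defines as d of at least 0.5.

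**The concern.** There are two separate issues.

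The first is efficiency. A cut at 4 puts patients with 1 to 3 adverse experiences together with those who have none. A cut at 33 treats a PCL-5 of 34 like one of 70. If the effect is graded, the interaction test discards information that has already been collected, and interaction tests usually have less power than the main effects beside them.

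The second is timing, and it concerns the PCL-5 alone. The analytic plan ties the BMI covariate to admission but attaches no date to the PCL-5 group, which it describes as current symptoms. If a discharge or follow-up value defined the group, patients whose PTSD symptoms fell with treatment would enter the low group. Where PTSD symptoms and eating symptoms improve together, the high group would then appear to improve less, even if admission PTSD had no effect. That is the direction the trial hypothesises, so an artefact would look like confirmation.

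**Working it through.** **1. The plan's own figure.** The inputs given are N=100, the statement "Based on an expected effect size of at least *d*=0.5", and an allowance "to account for a range of potentially inflated intraclass correlation coefficients that could reduce power". The 0.5 is defined elsewhere as "pre- to posttreatment change with at least a medium Cohen *d* effect size of 0.5"; no size is given for the interaction. Alpha, power, the ICC values and the group split are not stated, so 100 cannot be rebuilt. For orientation, at an assumed two-sided alpha of 0.05:

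- Pre-post main effect: n = ((1.960+0.842)/0.5)² = 31.4, so 32 patients for 80% power. N=100 is ample.
- Two-group difference in change of 0.5 SD of change: n per group = 2×(2.802/0.5)² = 62.8, so 63 per group, 126 in all. With N=100, power is Φ(0.5/√(1/n₁+1/n₂) − 1.960): 71% at 50:50, 63% at 30:70, 52% at 20:80.
- If the 0.5 is in raw SD units, the SD of change is √(2(1−ρ)), and power at 50:50 is 56%, 71%, 90% and 98% for ρ = 0.3, 0.5, 0.7 and 0.8.

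The margin for the interaction may therefore be thin or comfortable, depending on inputs that the article does not give.

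**2. Information lost by the cut.** For a normal score with a linear effect, the efficiency of a cut with proportion p on one side is the squared correlation of score and indicator, φ(z_p)²/[p(1−p)]. If the test on the score has 80% power, the test on the cut has power Φ(2.802×√efficiency − 1.960).

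| Split | Efficiency | Lost | Power, if 80% on the score |
|---|---|---|---|
| 50:50 | 0.1592/0.25 = 0.637 | 36% | 61% |
| 30:70 | 0.1209/0.21 = 0.576 | 42% | 57% |
| 20:80 | 0.0784/0.16 = 0.490 | 51% | 50% |

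With N=100, the binary test is worth 64, 58 or 49 patients analysed on the score. At 10:90 the loss is 66%.

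Neither score is exactly normal, so both were also simulated. For a PCL-5 bounded at 0 and 80, with assumed mean 25 to 50 and SD 17 to 20, the cut at 33 loses 33% to 55%. For a 0-10 ACES count with assumed mean 2 to 4, the cut at 4 loses 32% to 35%.

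**3. Which PCL-5 value defines the group.** If the cut sat at the admission mean and PCL-5 fell by 0.5 SD with unchanged spread, the share above it would go from 50% to Φ(−0.5) = 31%, a net 19 points.

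To see what this could do, 4,000 trials of 100 patients were simulated with no moderation by admission PCL-5. The assumptions were PCL-5 mean 40 and SD 18, a fall of 0.5 SD, PCL-5 retest correlation 0.6, outcome retest correlation 0.5, and a two-group comparison of change. Nominal error is 5%.

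| Residual PCL-5/outcome correlation | False positives, admission groups | False positives, discharge groups |
|---|---|---|
| 0 | 5% | 5% |
| 0.2 | 5% | 19% |
| 0.3 | 5% | 36% |
| 0.5 | 5% | 80-82% |

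About a third of the simulated patients changed group, in one direction or the other. The first row matters: with no residual correlation there is no bias.

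**The case against.** The best defence on timing is that the natural reading is already a fixed baseline group. The phrase about each timepoint attaches to the data, while it is patients who are divided. PCL-5 is called a predictor, the method is conventional moderation by interaction terms, and PCL-5 is left out of the outcome lists for the subgroup and moderation analyses. The word current can be read simply as the contrast to childhood history. A reader might infer that the plan regroups patients at follow-up. The article does not say so, and the baseline reading is at least as natural. What stands is that admission is never written for this variable, although it is for BMI, and that the wording allows either reading. Same-visit grouping in the cross-sectional t tests would not itself bias the moderation analysis.

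On the cuts, the defence is that they are prespecified and that the PCL-5 threshold is cited, so they are not data-driven. The dose-response remark is background on adult illness, not a hypothesis of this trial, and the trial's own ACES sentence already puts patients with few experiences beside those with none. The primary hypothesis is itself worded by group. All of this is fair. Dichotomising is therefore a less efficient choice that sits uneasily with the graded language, not a formal contradiction.

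A reader might also extend the timing point to the ACES. That is not supported: the ACES records childhood events, which treatment cannot change.

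**Conclusion.** The point holds as a worthwhile improvement plus one clarification.

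The cuts cost about 36% to 51% of the moderation information for splits from 50:50 to 20:80. This rests on a roughly normal score and a linear effect. More extreme splits lose more, and a true threshold effect would mean less loss. The range is not a fact about this trial, because the article gives no distribution or split for either score. Nor does it show that the interaction tests are underpowered, since power at N=100 varies widely with unstated inputs.

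The PCL-5 group is undated. If a post-treatment value were used, spurious moderation could arise in the hypothesised direction, but only where changes in PCL-5 and in the outcome are correlated. The simulated error rates depend wholly on the assumed correlations. A reader might infer from the fall in the share above the cut that at least one patient in five must change group. The net shift is 19 points under the stated assumptions, and the gross movement depends on the retest correlation.

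**What to change.** - State that the PCL-5 moderator is the admission score in every moderation analysis.
- Enter admission PCL-5 and the ACES count as continuous, centred moderators in the moderator-by-time terms, including the quadratic time term if that model is retained.
- Present fitted changes at illustrative values, for example ACES 0 and 4 and PCL-5 20, 33 and 46.
- Keep the two prespecified cuts as a secondary descriptive analysis.

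The cost is analysis wording only. Table 1 already schedules the baseline PCL-5, the ACES count needs no new data, and the Results section places the start of analysis in the future. The downside is a linearity assumption for each moderator. Check it with a quadratic or spline term in the moderator; a two-group contrast cannot test it.

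### The trauma-history moderator is defined as four or more childhood adversities, so the analysis cannot test the broader trauma-history hypothesis it is meant to test

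*Protocol article*

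**What the plan says.** Three sections of the protocol article bear on this point.

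- **Introduction, Primary Hypotheses.** Treatment effects are expected to be moderated, in that "improvements in eating disorder symptoms will be less marked among those with a history of trauma or current PTSD symptoms". Neither the timing nor the number of traumatic exposures is restricted.
- **Methods, Secondary Outcomes: Comorbid Symptoms.** The ACES "is a 10-item self-report measure that assesses 10 types of childhood trauma, including physical, verbal, or sexual abuse, physical or emotional neglect". The list goes on with "having a parent who struggles with alcoholism, having a mother who is a victim of domestic violence, having a family member in jail", and ends with "having a family member diagnosed with a mental illness, and having a family member unavailable due to divorce, death, or abandonment". Its stated use as a predictor is graded: whether "patients with more ACEs have poorer outcomes compared to those with fewer or no ACEs".
- **Methods, A Priori Analytic Plan.** Patients are divided at a "threshold for history of trauma (defined as an ACES score ≥4") and, separately, at a threshold for "clinically significant levels of PTSD symptoms via the PCL-5 (PCL-5 ≥33"). Both splits feed independent-samples t tests at each timepoint and interaction terms in the mixed models.

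The article describes no measure of trauma exposure in adulthood.

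**The concern.** The hypothesis is about whether a patient has a trauma history. The rule that tests it asks whether a patient reports at least four kinds of childhood adversity. The two differ in two ways: the rule sets a minimum count that the hypothesis does not have, and it covers childhood only. Both differences put patients who have been exposed to trauma into the group below the threshold.

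The definition is how a hypothesis listed among the primary ones will be tested. A null interaction could be reported as showing that trauma history does not affect outcome, although most kinds of exposed answer pattern below the cut were never separated from the unexposed one. A positive interaction would show something about a heavy load of childhood adversity, and would not carry over to patients with one severe exposure or with adult trauma. The cut for the PCL-5 is described as the most commonly established one and is referenced; the article gives no reason for the ACES cut.

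**Working it through.** **Inputs.** Ten ACES items (Measures): three abuse types, two neglect types and five household items, 3 + 2 + 5 = 10. One point per item is an assumption, implied by the article's reference to the number of ACEs. The cut is ≥4 (A Priori Analytic Plan). The plan gives no figure of its own to reproduce here.

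**Step 1: single cases under the rule.**
- Physical, verbal and sexual abuse, nothing else: score 3, below the threshold.
- Trauma in adulthood only, no childhood items: score 0, below.
- Trauma in adulthood and four or more childhood items: above.

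**Step 2: all answer patterns.** There are 2^10 = 1,024.
- Below the cut: C(10,0) + C(10,1) + C(10,2) + C(10,3) = 1 + 10 + 45 + 120 = 176.
- At or above the cut: 1,024 − 176 = 848.
- Of the 176, one pattern has no item endorsed. The other 175 contain one to three of the types that the Measures section calls childhood trauma.
- Below the cut with no abuse item, that is, 0 to 3 of the other seven items: 1 + 7 + 21 + 35 = 64. So 176 − 64 = 112 patterns below the cut include at least one abuse type.

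These count possible answers. They show what the rule permits, not how many of the 100 participants are affected.

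**Step 3: does the other moderator close the gap?** The PCL-5 asks about symptoms over the previous month. It can pick up adult trauma that still causes symptoms, but it enters as a separate moderator, and past trauma without current symptoms is missed by both.

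**Step 4: illustration of dilution, on assumptions only.** Suppose the true moderator is binary, everyone above the cut has it, a share m of those below also has it, and misclassification is unrelated to outcome. The observed contrast is then (1 − m) times the true one. For a true contrast of d = 0.5, two groups of 50 and two-sided alpha 0.05 (all assumed for a simple two-group comparison):

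| m (assumed) | observed d | power |
|---|---|---|
| 0% | 0.50 | 0.71 |
| 20% | 0.40 | 0.52 |
| 40% | 0.30 | 0.32 |
| 60% | 0.20 | 0.17 |

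The article gives nothing from which m could be set. If the effect is graded by number of adversities, there is no single true difference to dilute. The table shows why the label matters; it does not estimate the loss.

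**The case against.** The best defence is that the protocol is open about what it does. It states the cut, describes the ACES as a childhood instrument, cites a dose-response relation between ACEs and adult illness, and says it will compare more ACEs with fewer or none. High versus lower adversity is a legitimate contrast. This stands, and it is why the cut need not be abandoned. It does not remove the mismatch, because the contrast is still labelled, and hypothesised about, as trauma history.

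Several stronger readings are tempting and are not supported.

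- *A reader might infer that patients with four household items and no abuse are wrongly placed above the threshold.* The Measures section counts all ten items as childhood trauma, so by the protocol's own terms they are placed correctly.
- *A reader might infer that every patient with adult trauma is placed below.* That holds only when the ACES score is also under 4. The protocol also speaks of patients below a threshold; it does not call them a no-trauma group.
- *A reader might infer that an ACES total would misclassify in the same way.* For childhood exposure it would not: three abuse types would score 3 and no longer be pooled with 0. That part of the problem comes from the cut. Adult-only trauma would still be missed.
- *A reader might infer a known loss of effect or power.* The rates needed are not in the document.
- *A reader might conclude that the cut should be replaced by any abuse, neglect or domestic-violence item versus none.* That is a debatable trade. Adult-trauma patients would remain in the reference group, a single endorsed item would define the exposed group, and the reference group could be small. If it held 10 of 100 patients (assumed), the standard error of the contrast in SD units would be √(1/10 + 1/90) = 0.333, against √(1/50 + 1/50) = 0.200 for an even split, or 67% larger. Data collection ended in May 2021, so it would also be a change made after the data were in.

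**Conclusion.** The point holds as a mismatch between hypothesis and definition. The plan hypothesises moderation by trauma history without restriction and tests moderation by a high count of childhood adversities. Patients with one to three listed types of childhood trauma, and patients with adult-only trauma and an ACES score under 4, are classed as below the threshold for trauma history. As defined, the analysis cannot support a conclusion about trauma history in general, whichever way it comes out.

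The classification result rests only on the item list, the stated cut and one point per item. The number of participants affected and the amount of any dilution are unknown. The ≥4 cut is usable under an accurate name.

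**What to change.** 1. In the A Priori Analytic Plan, rename the moderator high childhood adversity (ACES ≥4).
2. Narrow the moderation hypothesis in Primary Hypotheses, and any conclusion drawn from it, to childhood adversity. State that adult trauma exposure is not measured and that PCL-5 ≥33 covers current symptoms only.
3. Add the ACES total as a graded moderator in the mixed models, which matches the use described in the Measures section, and record when it was added.
4. Optionally, if item-level responses were kept, report an any-versus-none contrast on the abuse, neglect and domestic-violence items as a sensitivity analysis, labelled as added after data collection. It should not replace the ≥4 cut.

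Items 1 and 2 are wording changes and need no new data. Item 3 adds one set of interaction models over the eight outcome measures listed for moderation, with the extra tests that this brings. The main cost is a narrower claim. The article expected analysis to begin in April 2022; if it has begun, the changes should be reported with their timing.

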## Results

Recruitment of participants began in January 2019 and ended in February 2020. Data collection was completed in May 2021. Data analysis is expected to begin in April 2022, and results are expected to be published in fall 2022. The study was internally funded by ERC.

## Discussion

### Principal Findings

The treatment program described in this study is unique in that it is developed specifically for, and solely treats, patients with BESD at the residential level of care. It is expected that this program, tailored to the needs of patients with BESD, will result in improvement in eating disorder psychopathology, comorbid mood and anxiety symptoms, quality of life, and improvement in physiological measures of health as a result of changes in eating disordered behaviors.

Several practical challenges in evaluating real-world treatment make it important to develop a protocol and explicitly state a priori intentions and expectations. First, the lack of a control group makes it difficult to assess a program’s effectiveness. Nevertheless, our a priori hypotheses on the *degree* of improvement may help findings from this study aid in the development of treatment guidelines for other programs seeking to help adults with BESD, which is critically important given the increased prevalence of BESD compared to other eating disorders, and the medical complications unique to BED [30]. Second, because treatment is not conditional on consenting to provide research data, potential bias from evaluating a program based solely on voluntarily collected research data over time may occur. To mitigate this bias in this study, we prospectively created a protocol that would allow for consecutive admissions to the program to be evaluated without the need for an additional research overlay that may lead to missing data in a biased fashion. Finally, because this is the first study to examine treatment for BESD at a higher level of care, it is important to clarify ahead of time exactly what treatment is being performed, what patients are admitted to the program, and what outcomes are expected as a result of treatment in the program.

